## 8. NUMBER OF SUBJECTS REQUIRED

The prevalence of histological chorioamnionitis during preterm PROM is 20 to 30% in the literature (1,10). Given that the mean of the index of high variation episodes (appendix 2, table 1) is in absolute value 3.82 in the case of chorioamnionitis and 1.18 in the absence of chorioamnionitis with a common standard deviation of 1.7, a sample of 60 analysable patients has a power of 95% to detect a significant difference in two-sided formulation and using a Student's t-test with a significant p less than 0.05 based on a prevalence of 15% of histological chorioamnionitis. Given the exclusion criterion for the analysis of the primary objective (delivery within 48 hours of the PROM, which concerns 50% of preterm PROM), a sample of 120 patients is required, 60 of whom can be analyzed for the primary objective.

Taking into account a safety margin of 30% (refusal to participate or presence of non-inclusion criteria), this study requires a minimum potential inclusion of 160 patients.

The planned recruitment is realistic. The annual numbers of pre-term POM at the CHU de Rennes, Angers, Nantes and Poitiers can be estimated at 100, 100, 100 and 60 respectively.

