## 9. STATISTICAL ANALYSIS

The predictive capacity of the index of episodes of high variation and the uni/multivariate indicator obtained from HRV parameters will be estimated on the basis of sensitivity, specificity, false-positive and false-negative rates, and the area under the ROC curve.

An exploratory univariate analysis of the parameters used to analyse HRV will be carried out. Comparisons of the distributions, means and medians of these parameters in the monitoring blocks associated with histological chorioamnionitis and in the blocks not associated with histological chorioamnionitis will be carried out (Student's *t* test and Mann-Whitney test).

Changes over time in the various parameters measured will be compared between the two populations using a 2-factor repeated time ANOVA (gestational age and chorioamnionitis). The subject effect will be included in the model to take account of the matched nature of the measurements.

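### The exploratory HRV comparison tests monitoring blocks with t and Mann-Whitney tests and makes no allowance for several blocks from one fetus, although the ANOVA in the same section does

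*Protocol*

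**What the plan says.** Section 9 of the protocol has three parts. The first estimates the predictive capacity of the index of episodes of high variation, and of a uni- or multivariate HRV indicator, by sensitivity, specificity, error rates and ROC area.

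The second is an analysis that the protocol itself calls exploratory: "Comparisons of the distributions, means and medians of these parameters in the monitoring blocks associated with histological chorioamnionitis and in the blocks not associated" with the condition. The named methods are Student's t test and the Mann-Whitney test. A monitoring block is not defined, and the number of blocks per fetus is not given.

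The third compares changes over time by a two-factor repeated-measures ANOVA, and adds: "The subject effect will be included in the model to take account of the matched nature of the measurements". That sentence belongs to the ANOVA only.

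Three other places bear on the point. Section 7.2 takes the chorioamnionitis diagnosis from the pathological examination of the placenta, which is one result per pregnancy. The same section collects fetal heart rate at inclusion and through the interval to birth. Section 3.1 defines the index from the last two recordings and the four before them, so a fetus with a calculable index has at least six.

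**The concern.** Recordings from one fetus resemble each other more than recordings from different fetuses. A two-sample test on pooled blocks counts each block as new information. The disease label does not vary within a pregnancy, so the information about its effect comes from the number of fetuses, not the number of blocks. The standard error is then too small, and parameters that do not differ are declared different too often.

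The protocol recognises the dependence one paragraph later and does not carry it back to these tests, so section 9 treats the same kind of measurement in two ways.

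At stake are the secondary HRV results. Sections 3.2 and 5.2 look for other parameters that could serve, alone or with the index, as an indicator of chorioamnionitis. Few cases are expected and many parameters are considered, so spurious differences could mislead the choice among them.

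**Working it through.** **The protocol's own figure.** No error rate or power is stated for the block comparison. The only power figure, in section 8, is for the patient-level index: means of "3.82 in the case of chorioamnionitis and 1.18 in the absence of chorioamnionitis with a common standard deviation of 1.7", two-sided 5%, 60 analysable patients, "based on a prevalence of 15% of histological chorioamnionitis". That gives 0.15 × 60 = 9 cases and 51 non-cases. The standardised difference is (3.82 − 1.18)/1.7 = 1.55, and the noncentrality is 1.55 × √(9 × 51/60) ≈ 4.3 on 58 degrees of freedom. Power is 98.8%, against the 95% stated. The stated figure is on the cautious side and has no bearing on the block tests; only the 9 and 51 are carried forward.

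**Inputs for the block tests**
- Fetuses: 9 and 51, borrowed from section 8. Section 9 does not say which patients enter this comparison.
- Blocks per fetus, m: not stated. Base case 6 (the 2 + 4 recordings of the index); range 2 to 20. Assumption.
- ICC between blocks of one fetus: not stated. Range 0.1 to 0.7. Assumption.

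**Reading A: all blocks of a fetus carry its placental label.** The variance of the difference in means is understated by the design effect DE = 1 + (m − 1) × ICC. The real two-sided error at a nominal 5% is 2 × [1 − Φ(1.96/√DE)]. For m = 6:
- ICC 0.1: DE = 1.5, 1.96/√1.5 = 1.60, error 11.0%
- ICC 0.2: DE = 2.0, 1.96/√2.0 = 1.39, error 16.6%
- ICC 0.3: DE = 2.5, 1.96/√2.5 = 1.24, error 21.5%
- ICC 0.5: DE = 3.5, 1.96/√3.5 = 1.05, error 29.5%

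Simulation with no true difference (3,000 data sets per setting) gave these errors for the block-level t test:

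| Blocks per fetus | ICC 0.1 | ICC 0.3 | ICC 0.5 | ICC 0.7 |
|---|---|---|---|---|
| 2 | 6.3% | 9.3% | 11.6% | 13.8% |
| 6 | 10.6% | 21.3% | 28.7% | 35.6% |
| 10 | 14.8% | 30.5% | 41.1% | 46.7% |
| 20 | 25.3% | 46.5% | 54.3% | 60.8% |

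The Mann-Whitney test was within about one percentage point throughout. A t test on one mean per fetus stayed between 4.0% and 5.8% in every setting.

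**Reading B: only the last two of six recordings of a case count as associated, and all other blocks are pooled.** The groups then hold 9 × 2 = 18 and 9 × 4 + 51 × 6 = 342 blocks, and each case supplies blocks to both. With unit variance and ICC 0.5:
- Variance of the first mean: (1 + 0.5)/18 = 0.0833
- Variance of the second mean: [342 + 0.5 × (9 × 4 × 3 + 51 × 6 × 5)]/342² = 0.0099
- Covariance: 0.5 × (9 × 2 × 4)/(18 × 342) = 0.0058
- True variance of the difference: 0.0833 + 0.0099 − 2 × 0.0058 = 0.0816
- Variance assumed by the test: 1/18 + 1/342 = 0.0585
- Ratio 1.39, 1.96/√1.39 = 1.66, error 9.7%

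Simulation gave 5.8%, 7.9%, 10.2% and 11.8% at ICC 0.1, 0.3, 0.5 and 0.7.

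**What this means for a list of parameters.** Section 2 names ten HRV parameters among its examples (SD, rMSSD, LF, HF, VLF, SD1, SD2, ApEn, SampEn, DFA-α1). If none differed, 10 × 0.05 = 0.5 would be expected to reach nominal significance. At 11% to 29% each, the expected number is 1.1 to 2.9.

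**The case against.** The strongest reply is that this is an exploratory step, labelled as such, and that no primary result depends on it. That stands. The primary criterion in section 5.1 uses one index value per patient, and section 8 powers that index.

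The second reply is that the size rests on quantities that the protocol does not give. That also stands. A reader might infer from the six-block rows that false-positive rates certainly rise several-fold. The text does not support this as a fact. At six blocks the rise is about two-fold at ICC 0.1 and reaches three-fold at about 0.2. With two blocks it is 1.3- to 2.8-fold, and under Reading B 1.2- to 2.4-fold over ICC 0.1 to 0.7. Reading B is not far-fetched, because the pilot changes in section 2 were seen in the last recordings before birth. If a block meant one set of recordings per fetus, there would be no inflation at all.

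Three further inferences go beyond the text:
- That every patient gives at least six recordings. Six is what the index needs, and the exclusion of deliveries within 48 hours applies to the main objective only.
- That these tests select the parameters for the indicator. Section 5.2 speaks of selected parameters but gives no selection rule, so misleading the choice is a risk and not a stated consequence.
- That the ANOVA is itself unsuitable because recordings fall at different gestational ages. It carries a subject effect, gestational age can be grouped, and how it is coded and fitted is ordinary SAP detail.

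None of this removes the structural point. The unit and the tests are named in the protocol, and the allowance for repeated measures is given to one analysis and not to the other.

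**Conclusion.** The point holds for the secondary, exploratory HRV comparison. Followed as written, the tests treat correlated blocks as independent. When all blocks of a fetus share one label, any positive within-fetus correlation pushes the false-positive rate above 5%; that direction does not depend on the assumed values.

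The size does. It is about 11% to 29% for six blocks per fetus, 9 against 51 fetuses and ICC 0.1 to 0.5. Under the narrower reading of associated blocks it is about 6% to 10% over the same ICC range, and about 12% at 0.7. The simulations gave every fetus the same number of blocks, so they do not measure the effect of longer stays contributing more blocks.

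This deserves correction before analysis, but it does not threaten the trial's main conclusion.

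**What to change.** Define the monitoring block: which recordings it covers, how many a fetus may contribute, and what makes a block associated with chorioamnionitis. Then make the fetus the unit in one of two ways:
- Apply the Student's t and Mann-Whitney tests to one pre-specified summary per fetus, for example the mean of the last two recordings.
- Keep the blocks and use a mixed model with a random fetus effect, or a cluster-robust test with fetus as the cluster.

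With only about 9 cases expected, the single summary is the simpler choice; in simulation it kept the error at 4.0% to 5.8%. Either way, section 9 would then treat matched measurements consistently.

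The cost is a few sentences and standard code, with no new data. P-values will be larger, and fewer parameters will appear to differ.

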| RESEARCH DURATION             | 
Length of inclusion period: 39 months
 
Maximum duration of participation for each patient/newborn pair: an average of 4 weeks of follow-up for the mother, and up to 15 weeks for the newborn, i.e. approximately 19 weeks.
 
Maximum total duration of the study: 50 months
                                                                                                                                                                                                                                                                                                                                                                                                                                                                                                                                                                                                                                                                                                                                                                                                                                                                                                                                                                                                                                                                                                                                                |

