After 34 weeks' amenorrhea (WA), there is no consensus on the appropriate course of action to be taken between expectant care with monitoring or a decision to give birth. However, before 34 WA, the management of preterm PROM consists of expectant care with close maternal-fetal monitoring in a high-risk pregnancy unit of a level appropriate to the gestational age. (15). On the other hand, if signs of chorioamnionitis are detected, the pregnancy should be terminated and the baby should be delivered urgently (16).

The strategies used to reduce the risk of chorioamnionitis in cases of preterm PROM are, on one hand, the systematic prescription of antibiotics and, on the other, close clinical and biological monitoring to detect its

occurrence as early as possible.

However, there is currently no specific marker for the early detection of chorioamnionitis:

- the clinical signs of chorioamnionitis are inconstant, variable, non-specific and usually occur at an advanced stage of infection (uterine contractions, hyperthermia, maternal and/or fetal tachycardia, uterus painful to palpation, foul amniotic fluid). (17).
- the positive predictive value of biological markers used in routine clinical practice is very low, particularly for CRP and hyperleukocytosis, which are the most widely used in France. The measurement of certain cytokines seems promising, but is still experimental and is not the subject of large series. Furthermore, although the sensitivity of these cytokines is interesting, none of them is specific for fetal or intra-amniotic infection (18).

A study carried out at Rennes University Hospital (Appendix 2) has shown for the first time that analysis of fetal heart rate (FHR) variability is a promising avenue of research in this indication.

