- short-term variation (STV): measures "micro" fluctuations in fetal heart rate and cannot be measured with the naked eye. It is independent of the baseline. STV is measured by dividing each minute of the trace into 16 sections of 3.75 seconds. The average pulse interval of each section is calculated and the change in these average values from one section to the next determines the STV.

Our previous single-center study carried out at the University Hospital of Rennes (Appendix 2, data not yet submitted for publication, pending patent registration) on a cohort of 23 patients with preterm PROM showed for the first time that analysis of the variability of the fetal heart rate (FHR) via Doppler collection of the cardiac signal is a promising avenue of research for screening for chorioamnionitis.

Certain parameters of FHR variability are modified in cases of histologically proven chorioamnionitis. These changes include an increase in baseline heart rate ( $p=0.02$ ), an increase in episodes of low variation ( $p=0.04$ ), a decrease in short-term variation ( $p=0.003$ ) and episodes of high variation ( $p < 0.001$ ) in the last recordings made before birth (spontaneous or induced) in cases of chorioamnionitis. The index of episodes of high variation (ratio of the mean number of episodes of high variation in the last two recordings to the previous four) appears to be a promising tool for the early diagnosis of chorioamnionitis in preterm PROM (sensitivity 90%, specificity 84.6%, positive predictive value 71.5%, negative predictive value 95.2%, area under the curve = 0.88, 95% confidence interval 0.73-100). These data are in line with those observed in cases of neonatal infection and are consistent with the underlying pathophysiological mechanisms (loss of variability, reduced foetal adaptability in response to the placental infectious/inflammatory stimulus).

These results therefore suggest that a prospective study should be carried out to test this index and to confirm the results for all the cardiac signals collected during the monitoring of preterm fetuses.

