### **4. DEFINITION OF ELIGIBLE SUBJECTS**

#### **4.1. Inclusion criteria**

The inclusion criteria are:

- adult patient
- singleton pregnancy
- PROM occurring between 26- and 34-weeks' gestation, authenticated on clinical examination and, if in doubt, confirmed by a vaginal diagnostic test detecting IGFBP-1.
- patient who has received information about the protocol and has not expressed opposition to participating.

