### 7.2. Research process

Inclusion will be prospective: any pregnant patient with a singleton pregnancy hospitalized for PROM between 26- and 34-weeks' gestation will potentially be included in the study.

Doppler recording of the FHR signal will be prospective from inclusion, as part of the routine of fetal well-being monitoring. Analysis of HRV parameters (index of episodes of high variation, linear and non-linear analysis) will be carried out using Matlab® software without the knowledge of the nursing staff. The algorithms for calculating these parameters have already been developed by the Signal and Image Processing Laboratory.

Clinical data will be collected prospectively in a relational events database. It will cover maternal, placental and neonatal data.

The Doppler data from the FHR signals, anonymized beforehand, will be stored progressively on a computer dedicated to the study. A copy of the signals acquired will be made regularly on the CIC-IT's secure server via the ASCENT system (Anonymized System for Clinical experimentation: <https://ascent.univ-rennes1.fr/>) and stored progressively on a database dedicated to the study.

In addition, a joint protocol has been drawn up with the investigating centres, setting out in particular the procedures for fetal heart rate recordings. This protocol does not significantly modify the current practices established in these centres, which are already harmonized.

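### The repeated-measures ANOVA on gestational age (Section 9) is poorly matched to a fetal series with staggered entry and exit and with the expected signal just before birth

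*Protocol*

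**What the plan says.** Section 9 names the method for the longitudinal comparison: changes over time are to be "compared between the two populations using a 2-factor repeated time ANOVA (gestational age and chorioamnionitis"). The next sentence adds: "The subject effect will be included in the model to take account of the matched nature of the measurements". It does not say whether that effect is random or fixed, whether gestational age is categorical or continuous, or whether a woman needs a complete series.

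Other sections fix the shape of the data:

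- **Entry.** Section 4.1 admits women with "PROM occurring between 26- and 34-weeks' gestation, authenticated on clinical examination".
- **Start of recording.** Section 7.2: "Doppler recording of the FHR signal will be prospective from inclusion, as part of the routine of fetal well-being monitoring".
- **Exit.** The fetal series ends at birth. The Summary gives "an average of 4 weeks of follow-up for the mother". Section 2 ties exit to the condition under study: "if signs of chorioamnionitis are detected, the pregnancy should be terminated and the baby should be delivered urgently".
- **Where the signal is expected.** Section 2 reports that the pilot changes were seen "in the last recordings made before birth (spontaneous or induced) in cases of chorioamnionitis". The primary index in Section 3.1 is built the same way: the last two recordings against the four before them.
- **Neonatal series.** Section 3.2 also covers the evolution of the neonatal parameters. Section 6 schedules the ECG by time since birth (48 hours, then weekly). Section 9 names no time factor except gestational age.

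**The concern.** A two-factor repeated-measures ANOVA in its classical form expects each subject to be measured at the same levels of the time factor. This study cannot supply that for gestational age. A woman whose membranes rupture at 27 weeks and another at 33 weeks may share no gestational week at all.

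The second problem does not depend on how the model is fitted. At a given gestational week the recordings come from some women who have just ruptured and others who are about to deliver. If chorioamnionitis changes the trace mainly in the days before birth, averaging by gestational age mixes recordings that should show the change with recordings that should not.

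At stake is the comparison of evolution with and without chorioamnionitis, the first of the two secondary objectives. A real change near birth could be missed or understated. The primary criterion and the sample size are not affected.

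**Working it through.** **Plan's own figure.** There is none for this analysis. The 95% power in Section 8 concerns a t-test on the index. Section 8 does supply the group sizes used here: 60 analysable women at 15% prevalence, so 0.15 × 60 = 9 cases and 51 non-cases.

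**1. How many women would have a complete series?**

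Assumptions, because the protocol gives no distributions:
- entry is uniform over 26 to 34 weeks;
- birth comes 2 days (2/7 week) plus an exponential interval with mean m weeks after rupture, with m = 4 taken from the average follow-up;
- the grid is weekly, and complete means a recording in each of weeks 26 to 33.

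A woman is complete only if she enters during week 26 (probability 1/8) and is undelivered at the start of week 33. With u the fraction of week 26 elapsed at entry:

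P = (1/8) ∫₀¹ exp(−(7 − u − 2/7)/m) du = (m/8) × exp(−(7 − 2/7)/m) × (exp(1/m) − 1)

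| m (weeks) | Calculation | P | Women of 60 |
|---|---|---|---|
| 2 | 0.25 × 0.0348 × 0.6487 | 0.6% | 0.3 |
| 4 | 0.50 × 0.1866 × 0.2840 | 2.7% | 1.6 |
| 6 | 0.75 × 0.3266 × 0.1814 | 4.4% | 2.7 |

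Simulation agrees (0.6%, 2.6% to 2.7%, 4.4%) and shows about 40% of the weekly cells filled at m = 4. Under uniform entry the complete share could not exceed 1/8, or 7.5 of 60, even if nobody delivered before week 34. At m = 4 the 9 cases supply about 1 to 5 women in any one week.

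**2. Does a more generous reading rescue the fit?**

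Yes, as far as fitting goes. A random-subject linear mixed model with continuous gestational age was fitted to 800 simulated trials of 60 women (9 cases, half-weekly recordings, staggered entry and exit). It converged every time and used every recording. The mean interaction estimates were −0.29 to −0.31 against a true −0.30, and the 95% intervals covered the truth in 93.5% to 95% of trials. This held when cases delivered twice as fast. In those data, however, the signal had been placed on the gestational-age axis. The result shows that the model can be fitted, not that the axis suits the protocol's hypothesis.

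**3. What does the axis cost if the signal lies near birth?**

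Same design, with the signal placed where Section 2 puts it: a drop of one residual standard deviation in cases, confined to the final week (size and window assumed), with a random intercept per woman and mean intervals of 2 and 4 weeks. Share of trials with p < 0.05:

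| Term tested with chorioamnionitis | Detected |
|---|---|
| Gestational age, linear | 23% to 30% |
| Time before birth, linear | 39% to 45% |
| Final-week indicator | 74% to 86% |

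A smaller run (60 trials per scenario) gave 13% to 22%, 40% to 48% and 72% to 85%, in the same order.

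The linear time-before-birth term recovers only part of the loss for a clear reason. For one woman, gestational age plus time before birth equals her gestational age at birth, so the two linear slopes mirror each other within her. The larger gain comes from letting the change concentrate near birth.

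**The case against.** The strongest reply is that the text does not commit to the classical fit. The subject-effect sentence can be read as a random effect, nothing demands complete series, and the choice between random and fixed may be made in an analysis plan that is not shown. This stands. A reader might infer that the ANOVA cannot be fitted soundly, or that it would discard most of the data. The documents do not support that, because it holds only under a complete-case rule that they never state.

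A reader might also infer that a fixed subject effect would remove the comparison, since chorioamnionitis does not vary within a woman. It absorbs only the chorioamnionitis main effect. Section 9 compares changes over time, which is the interaction, and that remains estimable. A check of 1,000 simulated trials with fixed subject effects gave a mean of −0.301 against a true −0.30, with 94.8% coverage.

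Nor is this the sole or leading secondary analysis. Section 9 also plans Student and Mann-Whitney comparisons between monitoring blocks, Section 5.2 mentions graphical and statistical modelling of the markers' evolution, and Section 3.2 does not rank its objectives.

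Finally, gestational age is a legitimate axis for describing maturation, and the primary index already captures change near birth. Both are fair, and they are reasons to keep gestational age in the model. They do not make it the right sole time factor for a comparison between women with and without chorioamnionitis: the index covers one parameter, while this analysis covers the others.

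**Conclusion.** The point holds as a mismatch between method and data, not as an impossibility. Two parts remain.

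- The named method, taken literally, needs a common gestational-age schedule that the study does not have. About 1 to 2 of 60 women would have a complete weekly series. This rests on assumed uniform entry, an exponential interval and a weekly grid, but the share stays below 5% for mean intervals of 2 to 6 weeks.
- Under the generous random-subject reading no recordings are lost, yet gestational age alone misaligns a signal that the protocol itself locates just before birth. With the assumed final-week drop, detection falls from 74% to 86% with a matched term to 23% to 30%. The matched term is a best case because its window equals the simulated one, and a different effect size or window would change the figures.

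The protocol names the method and the time factor, so this is a stated choice rather than a detail left open. It can be corrected without touching the design.

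**What to change.** In Section 9, replace the ANOVA sentence and the subject-effect sentence with a linear mixed model on all fetal recordings that has:

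- a random subject effect;
- gestational age as a continuous covariate;
- a chorioamnionitis by time-before-birth term as the comparison of interest, preferably non-linear or contrasting the last recordings with earlier ones. A linear term alone recovers only part of the loss.

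The form of the time-before-birth term should be fixed before the data are examined. The neonatal ECG series should be fitted in a separate model with postnatal age as the time axis.

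The cost is a few sentences and slightly more modelling, with no new data and no more patients. Time before birth is known only afterwards, so results on that axis describe what precedes delivery and must be interpreted as retrospective.
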